#### *Contrasts within study arm (paired design)*

Analyses will compare the true positive fraction between Stockholm3 and PSA, within either study arm. Comparisons will be made on a relative scale. rTPF is defined as  $TPF_{\text{Stockholm3}}/TPF_{\text{PSA}}$  or vice versa, as appropriate.

The rTPF (standard arm) is estimated as  $(a+b)/(a+c)$  (or  $(a+c)/(a+b)$ , as appropriate) and an approximate  $100(1-\alpha)\%$  two-sided confidence interval for rTPF is calculated as

$$\exp\left(\log(\widehat{rTPF}) \pm z_{\alpha/2} \sqrt{\frac{b+c}{(a+b)(a+c)}}\right).$$

Analogous formulas are used for comparisons within the experimental arm and for the relative False Positive Fraction.

Note: the quantity  $(a+b)/(a+c)$  estimates the rTPF in both the enrolled and randomised population. It also estimates the ratio of detection probabilities like  $\Pr(\text{ISUP} \geq 2, \text{Stockholm} \geq 11\% \mid \text{Experimental arm}) / \Pr(\text{ISUP} \geq 2, \text{PSA} \geq 3 \text{ ng/ml} \mid \text{Experimental arm})$ .

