### Primary endpoints

Contrasts between study arms: we will assess the non-inferiority of the experimental arm versus the standard arm in detecting ISUP $\geq 2$  cancers ( $\delta = 0.04$  or  $\exp(-\delta) = 0.78$ , as appropriate). The  $\alpha$  level is set to 0.025. Two-sided 95% confidence intervals will be reported.

Contrasts within study arms: we will assess the non-inferiority of the Stockholm3 test versus PSA in detecting ISUP $\geq 2$  cancers ( $\exp(-\delta) = 0.78$ ) and the superiority of PSA versus the Stockholm3 test in detecting ISUP1 cancers (i.e. a lower proportion of ISUP1 cancer detected according to the Stockholm3 test) ( $\exp(-\theta) = 1$ ). The  $\alpha$  level is set to 0.025 for both tests. Two-sided 95% confidence intervals will be reported.

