### Additional analyses

Due to updates in the Stockholm3 assay system to reduce measurement errors in the biomarkers included in the Stockholm3 risk prediction model, Stockholm3  $\geq 11\%$  as a selection criterion for randomization may be more sensitive than PSA  $\geq 3$  (i.e. more men with clinically significant prostate cancer will be randomized based on the criterion Stockholm3  $\geq 11\%$  compared with PSA  $\geq 3$ ). If this turns out to be true, we will perform analyses where we “count backwards” (increase the S3M cutoff) and compare biopsy rates at identical sensitivity for clinically significant prostate cancer when comparing diagnostic strategies involving S3M compared with PSA  $\geq 3$  (as described in Grönberg et al.).

We will artificially randomise (2:3) those men who screened negative on both screening tests. By doing this, the totals [d]+[h] and [d']+[h'] will become known, which in turn will allow the estimation of quantities like  $\Pr(\text{ISUP} \geq 2, \text{Stockholm3} \geq 11\% \mid \text{Standard arm})$  (i.e., the probability of ISUP  $\geq 2$  and Stockholm3  $\geq 11\%$  in enrolled men randomised to the standard arm). Contrasts between the two study arms with respect to these quantities will be

---

 Where applicable.

performed using the same methodology described in the section “Contrasts between study arms (unpaired design)”.

We may in additional analyses use regression models to model the DP, TPF, and FPF given covariates. We will employ standard generalised linear models or marginal models (Pepe and Alonzo 2001), as appropriate.

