#### Handling of missing data

Missing data with respect to outcome data (most importantly, participants who are recommended biopsy but never undergo the procedure) will primarily be handled by performing analyses on both the ITT and the PP populations. The analysis on the PP population inherently makes a missing-completely-at-random (MCAR) assumption. However, there is a chance that there is uneven dropout levels in the two arms. For example, men randomized to undergo MRI may to a higher degree choose to undergo biopsy since there is visual feedback of a lesion. If deemed necessary to understand and interpret study results, we may therefore perform multiple imputation based on the Stockholm3 score to impute outcomes for men who drop out of the study before the biopsy is performed. Briefly, if imputation is performed, it will follow the following protocol:

- *Systematic biopsy arm.* The Stockholm3 test, which is calibrated to systematic biopsy outcomes, will be used to impute biopsy outcome on men who did not undergo biopsy (despite a study recommendation to do so) by performing a Bernoulli experiment using the predicted Stockholm3 risk score for ISUP 2 cancer as a parameter. The analysis will be performed on 1000 multiple imputation datasets and summarized.
- *Experimental biopsy arm.* We will, by using data with the STHLM3MRI trial, fit a model to associate Stockholm3 test and PI-RADS score result to TBx outcome (Stockholm3-TBx). Using this model, we will proceed in a similar way as for the control arm. I.e., we will repeatedly impute outcome using Bernoulli experiments with the predictions from the Stockholm3-TBx model as parameter. The analysis will be performed on 1000 multiple imputation datasets and summarized.

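### The optional imputation of missing biopsy results has no separate PSA term, so it can be a biased robustness check of the Stockholm3-versus-PSA contrasts

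*Combined protocol and SAP*

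**What the plan says.** SAP, Handling of missing data: missing biopsy outcomes "will primarily be handled by performing analyses on both the ITT and the PP populations". Imputation is a conditional extra, to be done only if judged necessary for interpreting the results: "we may therefore perform multiple imputation based on the Stockholm3 score to impute outcomes for men who drop out of the study". The reason given is that drop-out may be uneven between the arms. No trigger is defined, and no alternative imputation model is named.

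If imputation is done, a control-arm man without a biopsy gets his outcome "by performing a Bernoulli experiment using the predicted Stockholm3 risk score for ISUP 2 cancer as a parameter". In the experimental arm the plan is to "fit a model to associate Stockholm3 test and PI-RADS score result to TBx outcome" using this trial's data, and then to draw from the predictions. PSA is not a separate predictor in either arm. The SAP's Design section does list total PSA, free PSA and their ratio among the components of the score.

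On the comparison itself, the SAP section on contrasts within study arm states: "Analyses will compare the true positive fraction between Stockholm3 and PSA, within either study arm". Under Primary endpoints, within arms, "we will assess the non-inferiority of the Stockholm3 test versus PSA in detecting" ISUP ≥2 cancers, with margin 0.78 and one-sided alpha 0.025. Strategies 6 vs 3 and 5 vs 2 are within-arm contrasts in the experimental arm. Strategies 6 vs 1 and 5 vs 1 compare the arms, with Stockholm3 selecting men on one side and PSA on the other.

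**The concern.** An imputation model should contain the variables that define the comparison it feeds. Here the comparison classifies men by Stockholm3 ≥11% and by PSA ≥3, and only the first enters the imputation in its own right. Having PSA inside the score does not cure this, because it presumes that the score already extracts everything PSA has to say about biopsy outcome. That is close to the question under test.

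The within-arm ratio is (a+b)/(a+c), so Stockholm3 and PSA are separated only by the discordant cells b (Stockholm3-only) and c (PSA-only). In the control arm every imputed man in b has a probability of at least 11% and every imputed man in c has less than 11%, by definition of the cells. The SAP's Additional analyses section also refers to the 11% cut-off possibly being more sensitive than PSA ≥3 "Due to updates in the Stockholm3 assay system to reduce measurement errors in the biomarkers included in the Stockholm3 risk prediction model". This does not show that the score is miscalibrated, but it is a reason to check calibration before using the score as a fixed probability.

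At stake is the value of the imputed result as reassurance. It would be called on when drop-out had made the ITT and PP results hard to read.

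**Working it through.** **1. The plan's own power table.** Inputs (SAP, Updated sample size calculations): n = 6000, PSA detection rate DR 0.015–0.03, PSA sensitivity TPF 0.57–0.63, true ratio 1, margin 0.78, alpha 0.025, least overlap between the tests. With the SAP's variance, SE = √[(b+c)/((a+b)(a+c))] and power = Φ[−log(0.78)/SE − 1.96].

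First row (DR 0.015, TPF 0.57): a+c = 6000 × 0.015 = 90; diseased = 90/0.57 = 157.9; a = (2 × 0.57 − 1) × 157.9 = 22.1; b = c = 67.9. SE = √(135.8/8100) = 0.129, and power = 0.484 (stated 0.48). All 16 rows agree to within 0.005; the last is 0.868 (stated 0.87).

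**2. Experimental-arm ratio.** The documents give no figure for how far PSA ≥3 predicts detection beyond Stockholm3 and PI-RADS, so that odds ratio (OR) is an assumption. Simulated arm: 2100 × 3/5 = 1260 men, outcomes missing completely at random. Assumed population: logit Stockholm3 normal (mean −3.2, SD 0.9); log PSA normal (mean log 1.4, SD 0.68); correlation 0.6; positive MRI with log-odds 0.2 + 0.6 × (logit Stockholm3 + 2). Assumed outcome log-odds: −3.2 + 0.9 × (logit Stockholm3 + 2) + 2.2 × MRI-positive + log(OR) × (PSA ≥3 indicator − 0.8).

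Change in the Stockholm3/PSA ratio against complete data, imputing from Stockholm3 and MRI only, 20% missing:

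| OR for PSA ≥3 | Change |
|---|---|
| 0.5 | about −5% |
| 1 | about 0 |
| 1.5 | +2 to +3% |
| 2 | +4% |
| 3 | +6% |

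For OR 1.5 to 3 the change is +1 to +3% at 10% missing and +4 to +9% at 30%. With PSA ≥3 in the model, the change stays within 0.5%.

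**3. What a +4% shift would mean.** Hold the SE at its planned value and add log(1.04) = 0.039. In the first row, apparent power at a true ratio of 1 becomes Φ[(0.248 + 0.039)/0.129 − 1.96] = 0.603, against 0.484. One-sided error at the margin becomes Φ[0.039/0.129 − 1.96] = 0.049. In the last row (SE 0.081), power goes from 0.868 to 0.945 and the error is 0.070.

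**4. A second simulation, with imputation variance.** Assumptions: 975 PSA-positive and 262 Stockholm3-only men, 20% missing, 40 imputations combined by Rubin's rules, true ratio 0.78. With an informative PI-RADS in the model, the ratio rose by 0.01 to 0.02 (0.01/0.78 = 1.3% to 0.02/0.78 = 2.6%), and false non-inferiority stayed at or near 2.5%. If PI-RADS carried no information, the rise was 0.02 to 0.035 and false claims reached 4–12%. The ORs in step 2 are conditional on PI-RADS. The more of PSA's information PI-RADS absorbs, the closer that OR is to 1.

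**5. Strategy 6 vs 1, control side only.** Detection in PSA ≥3 is 18% (SAP, Basic data and assumptions); assume 20% missing. If the raw score averages 0.8 times true risk among the missing men: 0.8 × 0.18 + 0.2 × 0.144 = 0.1728, and the ratio is multiplied by 0.18/0.1728 = 1.04. At 1.25 times true risk: 0.8 × 0.18 + 0.2 × 0.225 = 0.189, multiplier 0.95. At 1.0 nothing changes.

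**6. Which way the raw score pulls in the control arm.** Assume 650 PSA-positive men (40–60% of them Stockholm3-positive), 175 Stockholm3-only men, and mean scores of 22% (both positive), 14% (Stockholm3-only) and 7% (PSA-only). True PSA-positive cancers: 650 × 0.18 = 117.

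At a 40% split, the imputed numerator is 260 × 0.22 + 175 × 0.14 = 81.7 and the denominator is 57.2 + 390 × 0.07 = 84.5, a ratio of 0.97. At 60% it is 110.3/104.0 = 1.06. Weighting 0.8 observed and 0.2 imputed, a true ratio of 0.78 gives (0.8 × 91.26 + 0.2 × 81.7)/(0.8 × 117 + 0.2 × 84.5) = 0.81 (0.83 at 60%). A true 1.0 gives 0.995–1.011, and a true 1.2 gives 1.16–1.18.

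**The case against.** The strongest reply is that this is a conditional analysis, subordinate to ITT and PP, on which no confirmatory test rests. PSA is inside the score. In the experimental arm, where 6 vs 3 and 5 vs 2 lie, the Stockholm3 effect is estimated from trial data, so a poorly predicting score would show as such. The motive for imputing is drop-out differing between arms, which does not bear directly on within-arm contrasts. All of this stands, and it limits the weight of the point.

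What remains is that the fitted model still sets the added effect of PSA status to zero, and that the control arm has no refit at all. PI-RADS protection is also incomplete: the section gives no rule for experimental-arm men without a PI-RADS score.

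A reader might infer more: that the imputation assumes Stockholm3 is right and would confirm it by construction. The documents do not support that. The bias is nil if PSA adds nothing and reverses if its added effect is negative. Step 6 shows the raw score pulling towards parity, which helps Stockholm3 if it is truly worse and hurts it if it is truly better. The control-arm ratio in that step (Strategy 4 vs 1) is also not among the contrasts named for the two main publications.

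**Conclusion.** The point holds in a limited form. The optional imputation rests on two untested assumptions: no added information from PSA status in either arm, and calibration of the raw score in the control arm. It can therefore mislead as a robustness check of 6 vs 3, 5 vs 2, 6 vs 1 and 5 vs 1.

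Size and direction are not settled by the documents. The step 2 percentages depend on an assumed joint distribution of Stockholm3, PSA and MRI result, and on data missing completely at random; they are ranges, not estimates for this trial. The error rates of 4.9–7.0% in step 3 need an OR of 2 and a fixed standard error, and step 4 found error near 2.5% when PI-RADS was informative. The 6 vs 1 range of 0.95 to 1.04 needs miscalibration of 0.8 to 1.25 times true risk and holds the experimental side fixed.

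Nothing here touches the ITT or PP results, or contrasts that select by PSA on both sides (3 vs 1, 2 vs 1) in the sense of favouring one blood test over the other.

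**What to change.** Amend the missing-data section so that any imputation used for 6 vs 3, 5 vs 2, 6 vs 1 or 5 vs 1 comes from a model fitted to the biopsied men of the same arm. Predictors: Stockholm3, log PSA and the four-way PSA/Stockholm3 cell (three cells occur among randomised men), with PI-RADS added in the experimental arm. Do not use the raw score as a fixed probability in the main imputed result. The Stockholm3-only imputation can be shown alongside as a sensitivity analysis. State what would trigger imputation and how men without a PI-RADS score are handled.

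All the variables are already collected. The cost is SAP wording, a little more code and slightly wider intervals, because the discordant cells would be estimated from trial data and not supplied by the score.

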## Hypotheses

### Overarching primary hypothesis

The overarching primary hypothesis of the STHLM3MRI trial is that a diagnostic pathway using the Stockholm3 test to select men for further workup using MRI followed by targeted biopsies and systematic biopsies in MRI positive men (S3M+MRI+TBx+SBx; Strategy 6) has non-inferior sensitivity for detecting clinically significant cancer (ISUP grade  $\geq 2$ ) and shows superior specificity (reduction in number of performed biopsy procedures and detected ISUP 1 tumours) compared with the diagnostic pathway using systematic biopsies in men with PSA  $\geq 3$  ng/mL (PSA+SBx; Strategy 1).

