| Maximum GS $\geq 4$ cancer core length | mm      | maximum length of Gleason $\geq 4$ cancer in any core                                                                                                                                       |
| Serious adverse events                 | Yes/No  | (1) Hospitalisation within 30 days after biopsy procedure, (2) infection treated with antibiotics within 30 days after biopsy procedure, or (3) death within 30 days after biopsy procedure |

*Independent variables*

| Variable                          | Measure | Comment                                        |
|-----------------------------------|---------|------------------------------------------------|
| Age                               | Years   | At referral creation                           |
| Previous prostate biopsy          | Yes/No  | Patient self-reported                          |
| Family history of prostate cancer | Yes/No  | Any first degree relative with prostate cancer |
| PSA                               | ng/ml   | At blood test                                  |
| free PSA                          | ng/ml   | At blood test                                  |

|                       |                         |                       |
|-----------------------|-------------------------|-----------------------|
| Stockholm3 risk score | % risk of ISUP $\geq$ 2 | At blood test         |
| prostate volume       | ml                      | MRI defined           |
| PI-RADS               | 1–5 (integer)           | Maximum PI-RADS score |

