### Key secondary endpoints

Contrasts between study arms: we will assess the superiority of the standard arm versus the experimental arm in detecting ISUP1 cancers (i.e. a lower proportion of ISUP1 cancer detected in the experimental arm) ( $\theta = 0$  or  $\exp(-\theta) = 1$ , as appropriate). The  $\alpha$  level is set to 0.025. Two-sided 95% confidence intervals will be reported.

Contrasts within study arms: we will assess the superiority of PSA versus the Stockholm3 test in detecting ISUP1 cancers (i.e. a lower proportion of ISUP1 cancer detected according to the Stockholm3 test) ( $\exp(-\theta) = 1$ ). The  $\alpha$  level is set to 0.025. Two-sided 95% confidence intervals will be reported.

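### The optional imputation can adjust ISUP ≥2 for uneven biopsy uptake but cannot adjust ISUP 1, which is also part of the primary claim

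*Combined protocol and SAP*

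**What the plan says.** Under Handling of missing data, the SAP says that missing outcomes "will primarily be handled by performing analyses on both the ITT and the PP populations". It notes that the per-protocol analysis assumes data missing completely at random, and then that "there is a chance that there is uneven dropout levels in the two arms". Its example is higher biopsy uptake in the MRI arm, which is also Additional hypothesis 5. Imputation is the response, and it is discretionary: "If deemed necessary to understand and interpret study results, we may therefore perform multiple imputation based on the Stockholm3 score".

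The rule differs by arm.

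- **Standard arm:** the outcome is drawn "by performing a Bernoulli experiment using the predicted Stockholm3 risk score for ISUP 2 cancer as a parameter". The table of independent variables defines that score as a percentage "risk of ISUP $\geq$ 2".
- **Experimental arm:** the plan is to "fit a model to associate Stockholm3 test and PI-RADS score result to TBx outcome (Stockholm3-TBx"), then make Bernoulli draws in a similar way. The grade that counts as an outcome is not stated.

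The primary hypothesis joins non-inferior detection of ISUP ≥2 to superior specificity, and specificity is defined by fewer biopsy procedures and fewer ISUP 1 tumours. Under Key secondary endpoints, at alpha 0.025, "we will assess the superiority of the standard arm versus the experimental arm in detecting ISUP1 cancers". No ISUP 1 draw is described for either arm.

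**The concern.** Imputation would be used when uptake is uneven. A yes/no draw on the risk of ISUP ≥2 leaves every other imputed man as simply not ISUP ≥2, and it cannot say which of these men would have had ISUP 1. The remedy therefore reaches one part of the primary claim and misses another.

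In the ITT analysis a man who is never biopsied has no ISUP 1 diagnosis, so each arm's ISUP 1 proportion is scaled by that arm's uptake. If the MRI arm has higher uptake, a real reduction in ISUP 1 is partly hidden. If it has lower uptake, for example because men are lost at two steps (MRI, then biopsy), a reduction can appear where there is none. A reader could then see an uptake-adjusted ISUP ≥2 result beside an unadjusted ISUP 1 result.

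**Working it through.** **Check of the test formula against the plan.** The SAP attaches no figure to the imputation, so I used its power statement for Strategy 3 versus 1 (more than 90%).

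- About 1600 randomised men with PSA ≥3, split 2:3, give 640 and 960. After 20% dropout, 512 and 768 remain.
- The control rate is 18%. With rDP 1.3 the experimental rate is 23.4%. The margin is 0.04.
- SE = √(0.18×0.82/512 + 0.234×0.766/768) = 0.0228.
- Power = Φ((0.054 + 0.04)/0.0228 − 1.96) = 98%, which agrees with the plan.

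**Inputs for ISUP 1.**

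- Men: 640 control and 960 experimental, as above but before dropout, because ITT keeps everyone.
- ISUP 1 rate r among biopsied control men: not given. Protocol section 8.2 says about half of cancers found by systematic biopsy are low-risk, and the SAP gives 18% for ISUP ≥2. I assume 12–18%.
- Uptake by arm, u_c and u_e: not given, so assumed. The SAP gives only 20% dropout overall.
- True ISUP 1 ratio k (experimental/control at full uptake): 0.60 or 1.00, assumed.
- Uptake is taken as unrelated to outcome within each arm.

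**Formulas.** ITT proportions are p_c = r·u_c and p_e = r·k·u_e, so the expected ITT ratio is k × (u_e/u_c). With the SAP's Wald variance on the absolute scale (used for 3 versus 1), the chance of claiming ISUP 1 superiority is Φ((p_c − p_e)/SE − 1.96).

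**Direction the SAP expects: 75% control, 90% MRI arm, k = 0.60.**

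- Ratio: 0.60 × 0.90/0.75 = 0.72.
- r = 0.12: p_c = 0.0900, p_e = 0.0648, SE = 0.0138, power 45%.
- r = 0.18: p_c = 0.1350, p_e = 0.0972, SE = 0.0165, power 63%.
- Even 80% uptake, r = 0.12: 0.0960 and 0.0576, SE = 0.0139, power 79%.
- Even 80% uptake, r = 0.18: 0.1440 and 0.0864, SE = 0.0166, power 94%.

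**Reverse direction: 85% control, 75% MRI arm, k = 1.**

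- Ratio: 0.75/0.85 = 0.88.
- r = 0.12: 0.1020 and 0.0900, SE = 0.0151, false superiority 12%.
- r = 0.18: 0.1530 and 0.1350, SE = 0.0180, false superiority 17%. The nominal rate is 2.5%.

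**What ISUP ≥2 gets in the same settings.** With the SAP's rDP of 1.3, the ITT ratio is 1.3 × 0.90/0.75 = 1.56, or 1.3 × 0.75/0.85 = 1.15. If the draw worked as intended, it would bring both back towards 1.30. The stated rule offers no such step for ISUP 1.

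**The case against.** The strongest reply is that nothing primary is touched. Imputation is optional, sits behind ITT and per-protocol, and is introduced as a brief outline. ISUP 1 is reported in both main analyses, and the SAP is open about the assumption behind the second. This stands, and it limits the weight of the point. It does not supply a remedy for ISUP 1: ITT carries the uptake ratio, and the SAP itself doubts that the per-protocol assumption holds.

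Four stronger readings are tempting, and the documents do not support them.

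- *The plan has a 12–17% false-positive rate, or the imputation creates one.* The figures belong to the ITT contrast under assumed uptake and are the same whether or not imputation is run. They also need the direction the SAP does not expect. At 75% and 85% with no true effect, false superiority is 0.3% or less. At 82% and 78% it is about 5–6%.
- *The plan draws only ISUP ≥2 in both arms.* This is explicit for the standard arm only. For the experimental arm it is an inference.
- *Imputation frees ISUP ≥2 of uneven uptake.* It adjusts only given the score. The experimental model needs PI-RADS, which men without an MRI lack, and predicts the targeted result, although Strategies 3 and 6 use targeted plus systematic biopsies.
- *Imputed men must be recoded as biopsied.* The endpoint is whether a biopsy was performed, so for an unbiopsied man No is observed and not missing. Recoding it would change the estimand.

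The sizes above are for Strategy 3 versus 1. The uptake multiplier also enters 6 versus 1, but I have not sized that contrast. It does not enter 6 versus 3, which compares two tests within one arm and drove the final sample size.

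**Conclusion.** The point holds in a limited form. The stated rule cannot produce an ISUP 1 result, so the sensitivity analysis meant for uneven uptake serves ISUP ≥2 and leaves out an endpoint that is part of the primary claim and is tested between arms. This is a flaw of method in an optional analysis, and more than a missing detail; the ITT and per-protocol analyses stand as planned.

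In the direction the SAP expects, the bias left in ITT works against the specificity claim and the cost is power: 45–63% instead of 79–94% in the illustration. Only the reverse direction favours the claim. Both results rest on assumed uptake by arm, an assumed ISUP 1 rate of 12–18%, assumed true ratios, and uptake unrelated to outcome within arm.

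**What to change.** In Handling of missing data, state that any imputation will:

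- draw a three-level outcome (benign, ISUP 1, ISUP ≥2) in both arms, from models fitted to trial data within each arm;
- use the combined targeted-plus-systematic result where the strategy includes both;
- not require PI-RADS for men who had no MRI;
- report the ISUP ≥2 and ISUP 1 between-arm contrasts from the same imputed data sets.

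Keep biopsies as performed, and label that count as actual uptake when it stands beside imputed results. A full-uptake biopsy count would be supplementary only.

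The cost is SAP wording and slightly more modelling. No new data are needed, and no stated sample size or power figure changes.

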| 20200115 | Definition, intervention | Complete pathological report is defined as containing cancer/benign AND Global Gleason. For men in the experimental arm, this should hold for both pathological reports (TBx/SBx). For men with a “negative MRI” but STHLM3 $>25\%$ this should hold for SBx pathological report.                                     | 13.4  |
| 20200115 | Definition, intervention | Global Gleason Score is defined as the highest of Systematic and Targeted Bx global scores                                                                                                                                                                                                                            | 13.4  |
| 20200115 | Definition, intervention | Complete MRI is defined as existing MRI report including PIRADS score.                                                                                                                                                                                                                                                       | 13.4  |

|            |                              |                                                                                            |      |
|------------|------------------------------|--------------------------------------------------------------------------------------------|------|
|            |                              | Complete MRI is mandatory for inclusion of experimental arm men in the PP.                 |      |
| 20200115   | Definition, Study population | Study population is defined as participating men. See further in Statistical Analysis Plan | 13.4 |
| 2020-01-29 | Definition, Study population | Participating men are defined as men with registered consent and blood sample.             | 13.4 |
|            |                              |                                                                                            |      |

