## Post-hoc analyses

Ignoring biopsy results on men with negative MRI and Stockholm3  $\geq 25\%$

In order to estimate results in the counterfactual scenario where participants with negative MRI and Stockholm3  $\geq 25\%$  would not have been referred to undergo systematic biopsy, we will perform analyses where these biopsies are ignored. To be clear, we will not exclude these men from the analyses, but ignore their biopsy and biopsy outcome (i.e., they would enter the analyses as not having had a biopsy or any potential cancer diagnosis). The participants with a negative MRI and Stockholm3  $\geq 25\%$  will in these analyses thus contribute to the counts of performed MRI scans, but not to the count of biopsies or the cancer count. Apart from this, the analyses will be performed identically as detailed above.

## Appendix 1

Let  $T$  and  $S$  be the events “SBx+TBx positive for a specific ISUP grade” (eg, ISUP $\geq 2$ ) and “SBx positive for a specific ISUP grade”, respectively. Let  $P$  be the event “PSA screening test above 3 ng/ml”. Let  $D$  be the event “the subject is positive for a specific ISUP grade (true, unobservable status)”.

The main between-arm contrast of Study 1, expressed in relative terms, is given by

$$\frac{\Pr(T = 1|P = 1)}{\Pr(S = 1|P = 1)}.$$

This can be rewritten as:

$$\begin{aligned} \frac{\Pr(T = 1|P = 1)}{\Pr(S = 1|P = 1)} &= \frac{\Pr(T = 1, D = 1|P = 1) + \Pr(T = 1, D = 0|P = 1)}{\Pr(S = 1, D = 1|P = 1) + \Pr(S = 1, D = 0|P = 1)} \\ &= \frac{\Pr(T = 1, D = 1|P = 1) + \Pr(T = 1|D = 0, P = 1)\Pr(D = 0|P = 1)}{\Pr(S = 1, D = 1|P = 1) + \Pr(S = 1|D = 0, P = 1)\Pr(D = 0|P = 1)} \quad [\text{assumption}] \\ &= \frac{\Pr(T = 1|D = 1, P = 1)\Pr(D = 1|P = 1)}{\Pr(S = 1|D = 1, P = 1)\Pr(D = 1|P = 1)} = \frac{\Pr(T = 1|D = 1, P = 1)}{\Pr(S = 1|D = 1, P = 1)} = r_{TPF} \end{aligned}$$

The third equality holds under the assumption that the FPFs  $\Pr(T = 1|D = 0, P = 1)$  and  $\Pr(S = 1|D = 0, P = 1)$  are equal to zero, while the fourth equality hinges on the fact that — because of randomisation — the probabilities  $\Pr(D = 1|P = 1)$  in the two study arms are the same in expectation.

The equation above can be extended to the other between-arm contrasts.

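### The optional imputation models targeted-biopsy outcome only in the experimental arm, which is the wrong endpoint for Strategies 3, 6 and 9, and gives no prediction for men without an MRI

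*Combined protocol and SAP*

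**What the plan says.** The SAP, Handling of missing data, deals with missing outcomes mainly by reporting both the ITT and the PP population. It notes that PP assumes data missing completely at random and that dropout may differ between arms, and then adds: "If deemed necessary to understand and interpret study results, we may therefore perform multiple imputation". The men to be covered are described through "multiple imputation based on the Stockholm3 score to impute outcomes for men who drop out of the study before the biopsy is performed".

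- **Control arm.** "The Stockholm3 test, which is calibrated to systematic biopsy outcomes, will be used to impute biopsy outcome on men who did not undergo biopsy", by "performing a Bernoulli experiment using the predicted Stockholm3 risk score for ISUP 2 cancer as a parameter".
- **Experimental arm.** The plan is to "fit a model to associate Stockholm3 test and PI-RADS score result to TBx outcome (Stockholm3-TBx"), then to draw outcomes from its predictions.

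Each arm gets 1000 imputed data sets, which are then summarised. No parameter draws or pooling rule are stated.

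The experimental-arm endpoint is defined elsewhere. SAP Appendix 1 takes the event for the main between-arm contrast of Study 1 as "SBx+TBx positive for a specific ISUP grade". The protocol addendum (section 19) says the Global Gleason Score "is defined as the highest of Systematic and Targeted Bx global scores". The publications strategy makes Strategy 3 vs 1 the primary contrast of Publication 1, and 6 vs 3 and 6 vs 1 the contrasts of Publication 2. Strategies 3 and 6 both use TBx+SBx.

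**The concern.** The imputation is the one analysis the SAP offers specifically for dropout that differs between arms. For the main contrasts it would fill in a different endpoint from the one observed in men who completed work-up: TBx alone for the missing men, the higher of TBx and SBx for the rest. A man positive on TBx is positive on the combined result, but not the reverse, so the imputed detection probability can only be equal or lower.

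The model also needs a PI-RADS score, which an experimental-arm man has only if he had an MRI. Some of the men the analysis is meant to cover would get no imputed outcome. At stake is whether this sensitivity analysis could be interpreted if it were run.

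**Working it through.** **1. Size of the group.** SAP, Updated sample size calculations: about 2,100 randomised, 20% dropout. 2,100 × (1 − 0.20) = 1,680, which agrees with the stated figure of about 1,700. With 2:3 allocation, experimental-arm non-completers are 2,100 × 0.6 × 0.20 = 252.

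**2. Endpoint match.**

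| Strategies | Endpoint counted | Response in the stated model | Match |
|---|---|---|---|
| 3, 6, 9 | TBx+SBx, higher grade | TBx | No |
| 2, 5, 8 | TBx | TBx | Yes |

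The mismatch affects contrasts 3 vs 1, 6 vs 1, 6 vs 3 and 9 vs 7.

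**3. Size of the under-detection.** Inputs from the documents:
- MRI-positive share 1 − 0.55 = 0.45 (protocol section 19)
- control detection 0.18 (SAP, original sample size)
- rDP 1.3 (SAP, updated sample size), so experimental detection is 0.18 × 1.3 = 0.234
- dropout 0.20

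Assumptions, not in the documents: TBx alone finds a fraction f = 0.75 to 0.95 of combined detection; 20% of MRI-positive men go unbiopsied, all after MRI; and all detections are in MRI-positive men.

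Bias = 0.45 × 0.20 × (0.234 / 0.45) × (f − 1) = 0.20 × 0.234 × (f − 1)

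- f = 0.95: −0.0023, about −0.2 points
- f = 0.75: −0.0117, about −1.2 points

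The 0.45 cancels. If half of that loss came before MRI, the model would apply to half as many men: 0.10 × 0.234 × (f − 1) = −0.1 to −0.6 points. The figure scales with the loss rate among MRI-positive men. It would exceed 1.2 points at f = 0.75 only if more than one in five of them went unbiopsied, which runs against the SAP's own expectation that seeing a lesion raises biopsy uptake.

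On the relative scale used for 6 vs 1, rDP is multiplied by 1 + 0.20 × (f − 1), that is 0.99 to 0.95.

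**4. Direction.** For 3 vs 1 the planned difference is 0.234 − 0.18 = 0.054. With this error alone it becomes 0.054 − 0.0023 = 0.052 to 0.054 − 0.0117 = 0.042. That is closer to the −0.04 margin, so the error is against the experimental arm. For 6 vs 3, which lies within one arm, a shortfall of the same proportion for both tests would largely cancel from the ratio; the response is still the wrong one.

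**5. Men the model does not reach.** Protocol section 19 defines a complete MRI as a report with a PI-RADS score. SAP, Study populations, keeps experimental-arm men in ITT with or without MRI. No rule covers a missing PI-RADS. If 25–75% of the 252 non-completers had no MRI (assumed), 252 × 0.25 = 63 to 252 × 0.75 = 189 men get no prediction. Separately, the PP definition expects only SBx for men with PI-RADS <3 and Stockholm3 ≥25%, so a TBx model has no response for them.

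**6. Control arm.** The score targets the right endpoint (SBx), but the section includes no comparison with observed SBx results. If the score were wrong by a factor c, control detection would shift by 0.20 × 0.18 × (c − 1). For c = 0.9 or 1.1 (illustration only) that is ±0.36 points. The documents give no value for c.

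**The case against.** **It is optional and secondary.** This stands. ITT and PP carry the results, and ITT already keeps every randomised man. No primary claim rests on the imputation.

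**TBx may be loose or left-over wording.** Plausible: the original sample size section writes S3M+MRI+TBx for a calculation it assigns to Strategy 6, and the SAP revision table records a change to the definition of TBx. But the Design section defines TBx as targeted biopsy and lists strategies with and without SBx, so an analyst following the text would fit the wrong response.

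**Men who skipped MRI may be outside the target.** The section first speaks of men recommended a biopsy who never have it, which in this arm could mean men already scanned. Its later wording, quoted above, is broader. On either reading these men are in ITT and no rule covers them.

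**Stronger readings.** Two might be inferred, and neither is supported.
- *The assay change shows the control score is miscalibrated.* The passage beginning "Due to updates in the Stockholm3 assay system to reduce measurement errors in the biomarkers" says the 11% cut-off may prove more sensitive than PSA ≥3. It does not say that calibration to SBx is lost.
- *The combined bias reaches about half the 4-point margin.* This adds 1.2 points to a control-arm error of 0.20 × 0.18 × 0.30 = 1.1 points. Both are assumed worst cases, and the score must also over-predict. If it under-predicted by the same amount, the errors would nearly offset (−1.2 against −1.1). The 4-point margin also applies only to the absolute contrasts; 6 vs 1 uses 0.78 on the ratio scale.

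**Conclusion.** The point holds for an optional sensitivity analysis. As written, the experimental-arm imputation uses the wrong response for Strategies 3, 6 and 9, cannot produce a value for men without MRI, and has no response to model for men with PI-RADS <3 and Stockholm3 ≥25%. The first defect understates experimental detection of ISUP ≥2 by about 0.2 to 1.2 points, given f of 0.75 to 0.95 and a 20% loss among MRI-positive men, all after MRI; it is less if some dropped out earlier. It cannot by itself produce a false claim of non-inferiority on ISUP ≥2. That statement does not extend to ISUP 1, for which the section gives no explicit rule.

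The control-arm weakness is an unchecked assumption, not a demonstrated error. A reader might infer that the ITT or PP results are biased by this plan; they are not, because neither uses the imputed values.

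**What to change.** In the SAP, Handling of missing data:

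- **(a) Response.** Match it to the strategy analysed: combined TBx+SBx ISUP ≥2 for Strategies 3, 6 and 9; TBx for 2, 5 and 8; SBx for men with PI-RADS <3 and Stockholm3 ≥25%.
- **(b) Missing MRI.** Keep PI-RADS as a predictor. For men without MRI, first impute PI-RADS from baseline covariates (Stockholm3, PSA, age, previous biopsy), then impute the biopsy result given that PI-RADS.
- **(c) Control arm.** Fit or recalibrate the model on the trial's own SBx outcomes with the same baseline covariates. Include PSA, since the trial compares PSA with Stockholm3.
- **(d) Uncertainty.** Redraw the fitted model parameters in each imputation and combine by Rubin's rules.
- **(e) Status.** Run it as a pre-specified sensitivity analysis beside ITT and PP, so that the decision to run it does not depend on results.

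Cost: SAP wording, modest programming and slightly wider intervals. No new data are needed.
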